#### Analyses of efficacy

The effects of treatment conditions on the various outcomes will be compared using an “intention to treat” approach. Data analysis will be performed using SPSS 12.0 software. The significance level (p) has been defined as 0.05. Results will be expressed as mean ± standard deviation (for quantitative data) or percentage (for qualitative data). The initial comparability of the three groups will be verified by ANOVA or Kruskal-Wallis test (if necessary) for quantitative data, and t test for qualitative data. Between groups quantitative data will be compared by Student’s test and qualitative data by Pearson χ2 test or Ficher’s exact test for small samples. Changes within groups will be assessed by t test and MacNemar χ2 for paired data for quantitative and qualitative data, respectively. There will be a post-hoc analysis of the dropout group and missing values. Patient characteristics of the dropouts will be compared to those of the group that complete each treatment.

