#### Inclusion criteria

Patients may be included if they are able to sign the informed consent form, and are aged between 18 and 55 years, with non-specific LBP lasting for at least 3 months without improvement, LBP leading to at least 1 month’s sick leave during the preceding year and/or 3 months’ sick leave during the preceding two years, and an open-ended or fixed-term contract of work in the public or private sector.

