#### Primary outcome measurement

The primary outcome of the trial is represented by the effectiveness of the impact of the mixed strategy on being able to work compared to FRP and AIP. Being fit for work is evaluated by the duration of sick leave in 1 year: the number of days’ sick leave during the preceding 12 months and during the 12 months of the study is collected for each patient and verified by checking with the health insurance provider.

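### Sick leave in the preceding 12 months is collected for each patient but left out of the comparison of arms, which costs precision on the primary outcome

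*Protocol article*

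**What the plan says.** Primary outcome measurement defines the endpoint: "Being fit for work is evaluated by the duration of sick leave in 1 year". The same sentence states that the number of days' "sick leave during the preceding 12 months and during the 12 months of the study is collected for each patient", and that it is "verified by checking with the health insurance provider". A verified baseline of the primary outcome is therefore planned for each patient.

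Analyses of efficacy then assigns a test to each step:

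- Comparison of arms: "Between groups quantitative data will be compared by Student", which the text completes as Student's test. No covariate, regression model or between-arm change score is named.
- Baseline: "The initial comparability of the three groups will be verified by ANOVA or Kruskal-Wallis test (if necessary) for quantitative data". For the other variables the sentence continues with a t test: "for quantitative data, and t test for qualitative data". No consequence for the efficacy comparison is attached to this check.
- Within each arm: paired tests of change.

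Inclusion criteria set only a floor on earlier leave, joined by an and/or: at least one month's "sick leave during the preceding year and/or 3 months" in the preceding two years. Screening for participation and randomization describes a computer-generated list and mentions no stratification by prior leave.

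**The concern.** Prior leave can enter the stated analysis in two places, the baseline check and the within-arm paired tests. Neither adjusts the difference between arms. Baseline spread could be wide: the entry rule admits a patient with no leave in the last year (three months in the year before) and one who was off for the whole year. If past leave predicts later leave, the unadjusted comparison leaves explainable variance in its standard error.

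Precision matters for both expected results in Hypothesis regarding the primary aims. The first is a significant difference between the mixed strategy and AIP. The second is the absence of a significant difference between FRP and the mixed strategy, which an imprecise comparison makes easier to obtain.

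Two lesser points sit in the same section. A t test compares two means and cannot compare categorical variables across three arms. And because patients are selected for recent sick leave, some fall in leave is to be expected in every arm through regression to the mean, so a paired test within one arm cannot separate that from benefit.

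**Working it through.** **Inputs from the article (Sample size):** target difference 30 days, alpha 0.05 (two-sided assumed), power 0.80, 60 per arm, 10% dropout. **Not given:** the SD of sick-leave days and the correlation r between prior-year and study-year leave. The SD is back-solved below. r is assumed to lie between 0.2 and 0.5. The SD of prior leave is assumed equal to that of the outcome.

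**Step 1, implied SD.** The 60 per arm cannot be reproduced without an SD, so the normal-approximation formula is inverted:

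SD = 30 / (1.960 + 0.842) × √(n/2)

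- n = 60: 10.71 × √30 = 58.65 days.
- n = 54 (if 60 already allows for dropout, 54/0.9 = 60): 10.71 × √27 = 55.64 days.

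These values follow from the stated design; they do not verify it.

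**Step 2, unadjusted standard error.** SE = SD × √(2/n) = 58.65 × √(2/60) = 10.71 days. With 55.64 and n = 54 the SE is again 10.71, so the powers in the table are the same on either reading.

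**Step 3, effect of ANCOVA.** Residual variance is multiplied by 1 − r², so SE(adjusted) = 10.71 × √(1 − r²), and power = Φ(30/SE − 1.96). For example, at r = 0.5: SE = 10.71 × √0.75 = 9.27; 30/9.27 − 1.96 = 1.28; power 0.899.

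**Step 4, effect of chance imbalance.** A 1.96-SE imbalance in prior leave is 1.96 × 10.71 = 21.0 days. With equal SDs, the part that reaches the unadjusted estimate is r × 21.0.

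| r (assumed) | 1 − r² | Adjusted SE (days) | Power for 30 days | n per arm for 80% (from 60) | Shift from a 21-day imbalance (days) |
|---|---|---|---|---|---|
| 0 (unadjusted) | 1.00 | 10.71 | 0.80 | 60 | 0 |
| 0.2 | 0.96 | 10.49 | 0.816 | 58 | 4.2 |
| 0.3 | 0.91 | 10.21 | 0.836 | 55 | 6.3 |
| 0.4 | 0.84 | 9.81 | 0.864 | 51 | 8.4 |
| 0.5 | 0.75 | 9.27 | 0.899 | 45 | 10.5 |

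**Step 5, check under skew.** Simulating gamma-distributed days (assumed mean 80, SD 58.65, 60 per arm, 30-day shift, no cap at 365) gave t-test power of 0.78 to 0.80. ANCOVA power was 0.82 and 0.89 at correlations of 0.3 and 0.5, set on the underlying normal scale. The gain is therefore not an artefact of assuming normal data.

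**The case against.** The strongest reply is that the arms are randomised, so chance imbalance is already in the unadjusted standard error and the type I error is not inflated. That stands. A reader might infer that an unadjusted test lets a difference in prior leave pass as a treatment effect. The article does not support this: there is no systematic bias, only a less precise estimate and one that depends more on the imbalance that happens to occur.

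A reader might also set the 21-day imbalance directly against the 30-day target and call it two thirds of the effect. That compares different quantities: 21 days is imbalance in prior leave, and only r times it reaches the estimate.

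Nor does the article establish that the trial starts short of power. A figure of about 76% arises only if 60 per arm is the number needed before dropout and 54 remain at an SD of 58.65. If 60 already includes the dropout allowance, 54 completers give 80%.

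Other fair points:

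- The SD is back-solved and r is unknown. At r = 0.2 the gain is only 1.6 percentage points.
- Skew and unequal variances are not shown to harm Student's test here. The arms are equal in size, and the simulated t test kept its power.
- The article does not say that change scores will be compared between arms, so faulting such a test would fault something not written.
- The t test for qualitative data may be a slip, since the next sentence gives chi-square and Fisher's exact test for between-group qualitative data. It is still wrong as printed.
- Covariate adjustment is often settled in an analysis plan, which is not at hand. But the article names the between-arm test itself, so this is a criticism of a stated choice. If a plan does specify adjustment, the two documents need to be reconciled.

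**Conclusion.** The point holds as one of efficiency. A verified baseline of the primary outcome is planned for each patient, and the stated comparison of arms does not use it. The unadjusted test is valid, so this is a worthwhile improvement and not a threat to the trial's validity.

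The gain is about 2 to 10 percentage points of power over r = 0.2 to 0.5, and its size rests on the back-solved SD, equal SDs in the two years and that assumed range of r. That the baseline is left out of the between-arm test rests on the text alone. It would be too strong to say that prior leave is not used at all, because it may serve the comparability check and the within-arm tests.

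The t test for qualitative data is a separate, definite misstatement. The caution on within-group changes concerns interpretation only, since the trial's stated hypotheses are between arms.

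**What to change.** - **Primary analysis.** State an ANCOVA of 12-month sick-leave days on arm and sick-leave days in the 12 months before randomisation, with robust or bootstrap 95% confidence intervals because day counts are likely to be skewed and are bounded. Fix the window explicitly: the article does not anchor the preceding 12 months, and treatment may begin up to 90 days after randomisation.
- **SF-36 and DPQ.** Adjust the between-arm comparisons for the baseline score.
- **Baseline check.** Replace the t test for qualitative data by chi-square or Fisher's exact test, or drop baseline significance tests and tabulate the arms.
- **Within-group changes.** Report them descriptively and do not present them as evidence of effect.

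The cost is wording, dated before outcomes are analysed by arm; Trial status says data collection was still under way at submission. No extra patients are needed. Prior leave is already to be collected and checked with the insurer. The only possible extra work is to re-extract it if it was recorded over a window that does not end before randomisation.

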### Interventions

The three treatment strategies last 5 weeks but the treatment content of each strategy is different. FRP involves 6 hours of treatment a day, 5 days a week in group of 6 to 8 patients. AIP includes individual rehabilitation with a private physiotherapist for 1 hour 3 times a week and individual exercises to be performed at home twice a week for 50 minutes. The mixed strategy includes AIP combined with 5 one-day group sessions. Patients are off work during the 5 weeks of treatment in all three groups.

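### Within-arm paired t tests of sick leave cannot show benefit, because entry selects on prior leave and no arm is untreated; their false-positive rate, and even its direction, is not fixed

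*Protocol article*

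**What the plan says.** The Analyses of efficacy section of the protocol article plans Student's test for quantitative data between groups and then adds: "Changes within groups will be assessed by t test", in paired form for quantitative data, with McNemar's test for qualitative data. The threshold is common to all tests: "The significance level (p) has been defined as 0.05". Sick leave is not named in the within-group sentence, but it is quantitative and has a before and an after value. Under Primary outcome measurement, "the number of days’ sick leave during the preceding 12 months and during the 12 months of the study is collected for each patient".

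The Inclusion criteria select on the before value: "LBP leading to at least 1 month’s sick leave during the preceding year and/or 3 months’ sick leave during the preceding two years". All three arms receive active treatment, and under Interventions: "Patients are off work during the 5 weeks of treatment in all three groups". The text does not say whether those 5 weeks count in the 12-month outcome.

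**The concern.** Patients who enter because their recent leave was high will, on average, have less leave in the following year even if treatment does nothing. A paired test against the entry-year value counts that drift as change. With no untreated arm, nothing in a single arm's before-after difference shows how large the drift is. The 5 weeks off work in every arm, if counted, push the after value up for a reason that is also not a treatment effect.

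The tests stand under an efficacy heading and are not labelled descriptive. The hypothesis section describes the expected benefit to participants as fewer days of leave, and the Background reports a 60% fall in one treated cohort followed before and after. A reader could take a significant within-arm fall as confirmation, or take significance in two arms but not the third as evidence that the arms differ.

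**Working it through.** **Inputs from the protocol.** 60 per arm; alpha 0.05 (two-sided assumed, since sidedness is not stated); entry at 1 month in the prior year and/or 3 months in two years (taken as 30 and 90 days); 5 weeks off work (35 calendar or 25 working days).

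**Not given.** The SD, the mean and the year-to-year correlation of sick leave. No figure is stated for the within-arm tests, so there is none to reproduce. The sample-size statement yields an SD only when solved backwards: SD = 30 × √(60 / (2 × (1.960 + 0.842)²)) = 58.65 days if 60 are evaluable. It serves here only as an anchor.

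**Step 1: how little drift is needed.** With SD 58.65 in both years and an assumed correlation of 0.5, the SD of the change is 58.65 × √(2 × (1 − 0.5)) = 58.65, and its standard error is 58.65/√60 = 7.57 days. Drifts of 10, 20 and 30 days are 1.32, 2.64 and 3.96 standard errors. The paired t test (noncentral t, 59 df) then shows a significant fall in about 25%, 74% and 97% of arms, against a nominal 2.5% in that direction.

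**Step 2: drift from the stated entry rule.** This is a simulation with no treatment effect. Yearly leave has the same distribution each year, with 20% or 40% zero-leave years and otherwise mean 60 days and CV 1.1, capped at 365. Three successive years are linked by a first-order autoregressive normal copula, and the full and/or rule is applied. The treatment weeks are not counted.

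| Correlation | Mean fall (days) | Arms with a significant fall |
|---|---|---|
| 0.3 | 25–32 | 59–81% |
| 0.5 | 19–26 | 44–68% |
| 0.7 | 12–17 | 28–45% |

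Repeat runs moved these by about a day or a few percentage points.

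**Step 3: counting the treatment weeks.** Adding 35 days to every after value leaves a significant fall in at most about 1% of arms and produces a significant rise in about 5–75%. Adding 25 days leaves a fall in at most about 9%.

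**Step 4: wider assumptions.** This covers 24 settings: gamma leave with pool mean 20, 40 or 60 days, shape 0.4 or 0.8, and latent correlation 0.3 to 0.85. The fall is about 4 to 30 days and is significant in 10% to 99.9% of arms (median about 48%; 17 of 24 settings at or above 30%). With 35 days added, a fall is significant in at most 1% and a rise in 5–100%. With no entry selection, the rate returns to about 2–3% in each direction, so the selection causes the excess.

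One setting in full (pool mean 40, shape 0.4, correlation 0.5): the mean goes from 84.9 to 61.9 days, a fall of 23.0, significant in 55% of arms. With 35 days added it goes from 85.1 to 97.0, a rise of 11.9, significant in 19%.

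**Step 5: comparing arms by their within-arm p-values.** If each of two identical arms shows a significant fall with probability p, they disagree with probability 2p(1 − p). At p = 0.534 this is 2 × 0.534 × 0.466 = 0.498. Over seven settings simulated without the treatment weeks, disagreement was 16–50%. In the same populations the between-arm Student's test rejected 4.8–5.2% of the time on follow-up days and 4.7–5.3% on change.

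**The case against.** The strongest reply is that the protocol does not rest on these tests. The primary outcome compares the mixed strategy with the other two, the sample size is for a difference between arms, and the main expected results are between-arm. The within-group sentence is a general line for all quantitative outcomes and never says that a within-arm fall will count as benefit. All of this stands: the randomised inference is unaffected, and the misreading is a risk, not something the plan commits to. It does not justify leaving an uninterpretable test of the primary variable, unlabelled, under an efficacy heading.

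Covariate adjustment might also be called a preference. It is indeed not needed for validity, since the unadjusted Student's test holds its level here. Adjustment uses data already collected to gain precision and to absorb chance imbalance in prior leave.

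A reader might infer that these tests will appear to confirm a decrease in every arm. The protocol does not support that: if the 5 treatment weeks count, a spurious fall becomes uncommon and a spurious rise is possible. Nor should the rate be taken from the one-month entry route alone, which gives 33–96%. The two-year route also admits patients with little leave in the prior year, and this lowers the figure. The simulations further assume no trend over time in untreated patients, which the protocol does not inform.

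**Conclusion.** The point holds in a limited form. For sick leave, the within-arm paired t tests are not valid evidence of benefit, because patients are selected on the before value and no arm shows the untreated course. With no treatment effect, the entry rule alone gives a mean fall of about 12 to 32 days and a significant fall in about 28–81% of arms under the distributions in Step 2, or about 10% to nearly 100% under wider ones. These figures assume that the treatment weeks are not counted. Counted as about 35 days, they can reverse the bias to a significant rise in about 5–75% of arms. How often the test misleads, and in which direction, cannot be settled from the protocol. The conclusion that it cannot be interpreted does not depend on the exact rate. The between-arm comparison is not biased by any of this, so the matter concerns how results are labelled and read.

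**What to change.** In Analyses of efficacy:

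- Report within-arm change in sick leave descriptively only, as a mean with confidence interval and a note that patients were selected on prior leave. Drop the within-arm significance test for this outcome.
- State that efficacy conclusions come only from between-arm contrasts of follow-up days. Replace the unadjusted Student's test with a comparison adjusted for prior-year days.
- In Primary outcome measurement, state whether the 5 treatment weeks count in the 12-month total.

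The cost is wording and a simple change of model. Prior-year days are already collected, so no new data are needed. Trial status reports data collection as ongoing with analysis still to come, so the change could be made before results are seen.

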#### Secondary outcome measurement

The secondary outcome of the trial is represented by the impact of the mixed strategy on quality of life and social ability compared to FRP and AIP. Quality of life and social ability are evaluated by the Short Form Health Survey questionnaire (SF-36) and the Dallas Pain Questionnaire (DPQ).

- The SF-36 is a self-administered questionnaire used to assess quality of life related to health [25,26]. This tool consists of 36 items grouped into eight dimensions, each corresponding to a different aspect of health: Physical Functioning; Role Limitations due to physical problems; Bodily Pain; General Health perceptions; Energy/Vitality; Social Functioning; Role Limitations due to emotional problems; and Mental Health. These 36 items allow evaluation with two summary scores: Physical and Mental Health Component Summary Scores (assessed by a score between 0 and 100, with higher scores indicating better quality of life).

- the Dallas Pain Questionnaire (DPQ) [27,28] is a self-administered questionnaire used to assess the amount of cLBP that affects four aspects (daily and work-leisure activities, anxiety-depression, and social interest) of patients’ lives. These four aspects are scored from 0 to 100% (higher scores indicating poorer quality of life).

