#### Observational follow-up

Assessments are undertaken in the rehabilitation center by an independent physiotherapist. Four stages of participant assessment are planned in this RCT (Figure 1):

- initial (T0) and end of treatment (T5w) assessments are performed during the seven days preceding the treatment and on the last day of treatment, respectively. These assessments include personal data, medical history, intensity of pain on the VAS, FFD, Ito, Sorensen and PILE tests, DPQ, FABQ, SF-36, HAD and WAI questionnaires.

- follow-up assessments are performed at 6 months and 12 months during the follow-up period. These assessments include interviews and clinical examination, intensity of pain on the VAS, FFD, Ito, Sorensen and PILE tests, DPQ, FABQ, SF-36, HAD and WAI questionnaires, number of days’ sick leave, patient diary (medical and paramedical interventions).

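### Intention to treat is promised for SF-36 and DPQ, but the named test uses only observed scores, missing values are left to a post-hoc analysis, and some patients are eliminated

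*Protocol article*

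**What the plan says.** All references are to the protocol article.

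- Analyses of efficacy sets the principle, "The effects of treatment conditions on the various outcomes will be compared using an “intention to treat” approach", and the test, "Between groups quantitative data will be compared by Student’s test". It names no repeated-measures model and no imputation.
- The same section deals with missing data in two sentences: "There will be a post-hoc analysis of the dropout group and missing values", and then "Patient characteristics of the dropouts will be compared to those of the group that complete each treatment".
- Sample size gives 60 patients per arm, 180 in total, and an estimated 10% dropout.
- Observational follow-up places data collection: "Assessments are undertaken in the rehabilitation center by an independent physiotherapist". SF-36 and DPQ are listed at the initial assessment (T0), at end of treatment (T5w) and later, where "follow-up assessments are performed at 6 months and 12 months during the follow-up period". No other route is described, although the SF-36 "is a self-administered questionnaire used to assess quality of life related to health" and the DPQ is self-administered too.
- Primary outcome measurement has sick leave verified with the health insurer. Secondary outcome measurement names no comparable source for SF-36 or DPQ.
- Concomitant treatments says that patients who receive a prohibited treatment are eliminated from the study. Withdrawal criteria lists the same event, for the 5-week course, and the development of a non-inclusion criterion.

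**The concern.** A Student's test can use only patients who have a score. With 10% dropout expected, that set differs from the set randomised, and the article does not say in advance how the gap will be handled. It calls the handling post hoc. This is a stated choice, so it cannot be read simply as detail left to a fuller document.

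Quality of life carries weight here. It makes up the secondary outcome together with social ability, and the section on the hypothesis lists it beside sick leave in both main expected results: a difference between mixed strategy and AIP, and none between mixed strategy and the functional restoration program (FRP). If patients who are doing badly are lost more often from one arm, that arm's observed mean is flattered and either contrast can move. The plan also leaves information unused. A patient lost after week 5 still has a T5w score that says something about the missing 12-month score, and a two-sample test at 12 months ignores it.

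Separately, eliminating patients after a prohibited treatment conflicts with intention to treat whatever the attendance.

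**Working it through.** **Inputs from the article.** 60 per arm; 10% dropout; scores at T0, T5w, 6 and 12 months. It gives no SD, target difference or arm-specific loss for SF-36 or DPQ, so there is no planned figure to reproduce for these outcomes. At 10% loss, 60 × 0.90 = 54 per arm remain.

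**Assumptions.** SD 20; true 12-month difference 5 points; correlation r between T5w and 12-month scores 0.5 or 0.7; higher score better (the SF-36 direction); loss after T5w follows a logistic curve in the standardised T5w score, with slope 0.25 to 1.5 log-odds per SD, set to give the chosen loss rate in each arm. The main scenario is 15% loss in AIP and 5% in mixed, which averages the planned 10%.

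**Formula.** Let m be the loss rate and g the gap in mean T5w score, in SD, between patients kept and patients lost. The mean of those kept exceeds the mean of all by m × g. At 12 months the excess is r × m × g. The bias in the mixed–AIP difference, a shrinkage here, is

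20 × r × (0.15 × g_AIP − 0.05 × g_mixed).

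| Slope | g_mixed (5% lost) | g_AIP (15% lost) | Bracket | Bias, r = 0.5 | Bias, r = 0.7 |
|---|---|---|---|---|---|
| 0.25 | 0.249 | 0.248 | 0.0247 | 0.25 | 0.35 |
| 0.5 | 0.494 | 0.484 | 0.0479 | 0.48 | 0.67 |
| 1.0 | 0.942 | 0.884 | 0.0855 | 0.86 | 1.20 |
| 1.5 | 1.297 | 1.167 | 0.1102 | 1.10 | 1.54 |

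The bias is therefore 0.25 to 1.54 points, or 5% to 31% of the true 5. Simulation under the same loss rates gives about 0.15 to 0.55 points for the shallow slopes and 0.7 to 1.6 for the steep ones. Roughly 0.2 to 1.6 covers both.

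**Against the noise.** With 60 × 0.85 = 51 and 60 × 0.95 = 57 patients, the standard error is 20 × √(1/51 + 1/57) = 3.85, so the largest bias is 1.54/3.85 = 0.40 standard errors. Power for a true 5 points is 0.25 without bias and 0.23 to 0.14 with it.

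**Other loss patterns.**
- Equal 10% loss with the same slope: 0.10g − 0.10g = 0. The observed-score standard error is about 1–4% larger than that of an estimator that also uses T5w.
- 12% v 8%: at most 0.6 points, even at slope 1.5.
- 25% v 10%: 1.3 to 2.2 points at the steep slopes, but this averages 17.5%, above the planned rate.

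**Alternative.** A likelihood estimator that uses T5w had bias below 0.1 points at 15% v 5% and below 0.2 at 25% v 10%, and its standard error was never materially worse. Near-zero bias is built into this set-up, because loss was made to depend only on the observed T5w score.

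**The case against.** This is a journal article, and imputation rules, the longitudinal model and follow-up of non-attenders commonly sit in a full protocol or analysis plan. That stands for whatever the article leaves unsaid. It does not cover what the article says, which is that missing values are a post-hoc matter.

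Several stronger readings are tempting, and the text does not support them:

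- **Testing visit by visit on attenders only.** The article does not say this. It names a test that needs observed scores and no model that would recover the others.
- **AIP patients will attend less because they are treated elsewhere.** This is conjecture. All arms have assessments at the same centre, the diary is collected at the same follow-up appointments, and one dropout rate is given for all. The bias depends on a difference in loss that nothing in the article predicts.
- **The planned dropout comparison would usually miss the problem.** It has 52% power for a 0.5 SD difference (18 v 162). But the steep slopes imply T5w gaps in AIP of about 0.88 to 1.17 SD, for which power is 94% to over 99%. If only baseline scores are compared, the gap shrinks to about 0.44 to 0.82 SD and power is 42% to 91%. The valid point is that detecting a difference does not correct the estimate.
- **Patients who finish 5 weeks and then vanish count as completers.** The article does not define dropout, so this is a matter for clarification.

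It is also fair that the outcome is secondary and that, in this example, power is low even without bias.

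**Conclusion.** The concern holds in a limited form. The article promises intention to treat, names a test that uses observed scores only, and leaves missing SF-36 and DPQ values to a post-hoc analysis while expecting 10% dropout and having no outside source for these scores. A reader might go further and infer that the intention-to-treat comparison is certain to fail. The text shows only that it is not secured.

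The size is conditional. Bias arises if loss differs by arm and follows earlier scores: roughly 0.2 to 1.6 points of a true 5 at 15% v 5% loss, and about nil at equal loss. The SD, true difference, correlations, loss rates and slopes are all assumptions. The elimination of patients after a prohibited treatment needs none of them; it conflicts with intention to treat as written.

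**What to change.** 1. **Analyses of efficacy.** For SF-36 and DPQ, replace the separate Student's tests by one pre-specified linear mixed model. The outcomes are the T5w, 6- and 12-month scores; the terms are arm, visit, arm-by-visit and the T0 score as covariate. Include every randomised patient with any post-treatment score and read the 12-month contrasts from the model.
2. **Same section.** Define dropouts as patients without a 12-month score and report their number by arm.
3. **Withdrawal criteria and Concomitant treatments.** Reconcile these with the intention-to-treat statement, so that the outcomes of patients who receive a prohibited treatment are kept in the analysis.
4. **Optional, Observational follow-up.** Post the self-administered questionnaires to patients who do not attend.

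The first three changes need no new patients or visits. Trial status reports data collection ongoing and analysis still to come, so the wording could be settled before analysis. The model assumes data missing at random given the observed scores, which is weaker than what the observed-score test needs but still cannot be verified. Patients with no post-treatment score at all add nothing to it. Posting costs postage and introduces a slightly different setting for those answers.
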